#### Frequency-band analysis

2.5.4

For the frequency band analysis, the focus will be on analyzing the alpha and theta frequency bands during attentional tasks such as the Go-NoGo and PVT. This analysis aims to determine if there are correlations between task performance and changes in frequency bands, particularly if increased alpha band activity is associated with decreased task performance. In addition, we will examine whether the most significant changes in these frequency bands occur during the performance phases of the tasks or during inter-trial periods. To this end, we utilize a classification of trials into the following segments, as proposed by Pershin and colleagues (Pershin et al., 2023). They divided the trial phases *post hoc* into the five segments “perception/memory,” “preparation,” “perception/action,” “reset” and “relax.” Figure 3 illustrates an example sequence of a single trial. For the frequency band analysis, power spectral density (PSD) will be calculated using Welch’s method (Welch, 1967) with further processing by the FOOOF (Fitting Oscillations and One Over F) package (Donoghue et al., 2020) to extract power values in predefined frequency bands (delta 1–4 Hz, theta 4–8 Hz, alpha 8–13 Hz, and beta 13–30 Hz).

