**Methods/design:**

The study “Studying Neurocognitive Systems for Sustained Attention in Neurogeriatrics Patients” (SENSE-AGE) is a prospective, explorative, observational study and will include 120 geriatric participants. At admission, participants will perform a Go-NoGo task, a Psychomotor Vigilance Task (PVT) and resting-state condition during EEG recording, using a 32-channel system. Task-based event-related potentials (ERPs) and frequency-band power will be extracted. Neuropsychological tests characterize global and domain-specific cognition and will examine associations between sustained attention, broader cognitive performance, and EEG parameters. Questionnaires will assess fatigue, sleep, health-related quality of life, and subjective cognition. A subgroup of 50 participants will be re-evaluated at the end of the inpatient stay, after 2–3 weeks of standardized geriatric complex treatment. The main hypotheses of the study are: sustained attention (i) correlates with ERP amplitude and latency; (ii) correlates with EEG power; (iii) improves after an inpatient multiprofessional complex treatment at both the task-performance and neurophysiological level.

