The findings of Pershin et al. (2023) challenge the existing theories by suggesting that changes in sustained attention are less related to the actual performance of a sustained attention task, but are instead more closely associated with phases between subsequent trials in such task—which they describe as recovery phases. They demonstrated that electrophysiological markers such as alpha power changes within the sustained attention task, exhibited the greatest observed changes during intertrial intervals, where no response was required. This suggests that these intervals may represent phases when the brain is recovering from task-related demands (Pershin et al., 2023). We suggest that increased stress levels, which may occur when cognitive tasks require more “brain effort” in older adults, could further exacerbate sustained attention deficits by disrupting recovery phases, leading to a vicious cycle of reduced attention and increased stress (Selye, 1978; Wippert et al., 2009; McAvinue et al., 2015; Dillard et al., 2019; Luna et al., 2022; Buzsáki et al., 2003).

The combination of psychometric tests and EEG enables the concurrent evaluation of the correlation between behavioral responses and neural activity (Olbrich et al., 2015). In a general sense, EEG can be analyzed along the time domain and the frequency domain. Previous research has employed EEG parameters to investigate temporal differences in processing and responding to stimuli during sustained attention tasks. Event-related-potential (ERP) latency and amplitude parameters, as well as power changes in the alpha and theta bands, are directly related to attentional performance in older adults (Finnigan and Robertson, 2011; Vaden et al., 2012; Staub et al., 2014; Getzmann et al., 2016).

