Sustained attention will be measured with a 16-min cued Go-NoGo task on a computer [adapted from Pershin et al. (2023)]. Participants will see different pairs of pictures from the categories “animals,” “trees” and “fruits” (see Table 1) and have to react as fast as possible by pressing a button when two pictures with animals are shown (Go condition). In the NoGo condition, participants will see an animal as the first stimulus and a tree as the second stimulus, and have to inhibit their response (see Figure 3). The Ignore and Ignore & Novelty conditions will show two trees in a row or a tree and a fruit. No response will be required in these conditions. The presentation duration (100 ms), the interstimulus interval (1,000 ms) and the inter-trial interval will be controlled and the stimulus presentation will be randomized. Sustained attention performance in the Go-NoGo task will be quantified using several behavioral parameters. Median reaction time (RT) for correct responses in Go trials will serve as an index of sustained attentional performance. In addition, omission errors (failure to respond to Go stimuli, calculated as the proportion of missed Go trials) will be analyzed as indicators of attentional lapses, and commission errors (responses during NoGo trials, calculated as the proportion of false responses) as indicator of inhibitory control failures. Furthermore, discriminability (*d*’) will be calculated based on signal detection theory [*d*’ = Z(hit rate) – Z(false alarm rate)] to provide a bias-independent measure of sustained attention performance (Fortenbaugh et al., 2015).

**TABLE 1 T1:** The four different conditions of the Go-NoGo task.

Condition	Stimulus 1	Stimulus 2
Go	Animal	Animal
NoGo	Animal	Tree
Ignore	Tree	Tree
Ignore and novelty	Tree	Fruit

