#### Electroencephalography

2.4.4

EEG will be recorded in a laboratory environment to reduce and standardize external influences, such as light and noise. We will record EEG using a 32-channel layout connected to an actiChamp amplifier (BrainVision Brain Products GmbH). Electrodes will be placed according to the 10–20 system and online data collection will be done with an amplitude resolution of 0.1 μV and a sampling rate of 500 Hz, with online filters of 0.016–250 Hz. We aim for electrode impedances below 15 kΩ. EOG activity will be recorded using a single dedicated EOG electrode, placed below the left eye. Data will be recorded via the LSL protocol using the Lab Recorder (Kothe et al., 2024). Frequency bands will be analyzed during a subsequent 10-min resting period, divided into 5 min with eyes closed and 5 min with eyes open.

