#### EEG preprocessing

2.5.2

EEG data processing will be conducted using MNE (v1.3.1) (Gramfort, 2013) in Python (3.10). To ensure optimal ICA decomposition quality, a copy of the raw data will be high-pass filtered at 1 Hz (FIR, zero-phase), re-referenced to the common average, and used exclusively for ICA fitting. Noisy channels will be identified and interpolated using the PyPREP package (v0.4.2; (Bigdely-Shamlo et al., 2015)), followed by ICA decomposition. Artifactual independent components (e.g., ocular, cardiac, and muscle artifacts) will be identified using the ICLabel classifier (Pion-Tonachini et al., 2019) and confirmed by visual inspection. The resulting ICA weights and the list of excluded components will subsequently be applied to a separate copy of the raw data bandpass filtered at 0.1–30 Hz. This approach preserves slow neural activity below 1 Hz that is relevant to ERP morphology, following the recommendations of Winkler and colleagues (Winkler et al., 2015). The resulting cleaned, bandpass-filtered (0.1–30 Hz) data form the basis for all subsequent ERP and frequency-band analyses.

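### Task alpha is compared across trial phases without marking lid closure, so an inter-trial alpha rise could not be told apart from eyes being closed more often between trials

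*Protocol article*

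**What the plan says.** Section 2.5.4 (Frequency-band analysis) relates task alpha and theta to performance, "particularly if increased alpha band activity is associated with decreased task performance". It also asks whether the largest band changes "occur during the performance phases of the tasks or during inter-trial periods", using five trial segments of which 'reset' and 'relax' require no response. The Introduction gives the expected direction: in the model study, alpha "exhibited the greatest observed changes during intertrial intervals, where no response was required", which is read there as brain recovery.

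Section 2.5.2 (EEG preprocessing) sets out the route to the data: channel interpolation, ICA, component removal and a 0.1–30 Hz filter. The result is declared the basis of every ERP and frequency-band analysis. Eye activity enters only as artefact: "Artifactual independent components (e.g., ocular, cardiac, and muscle artifacts) will be identified using the ICLabel classifier", with visual confirmation. Section 2.5.1 names age, cognitive status, medication, depression, anxiety and mental fatigue as confounders; eye state is not among them.

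Eye state is separated at rest, where the 10 min are "divided into 5 min with eyes closed and 5 min with eyes open". Section 2.4.4 also states that "EOG activity will be recorded using a single dedicated EOG electrode, placed below the left eye", but gives that channel no role in detecting closure.

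**The concern.** The protocol separates eye state at rest and does not carry that distinction into the tasks. ICA subtracts the electrical potential of the eye and lid. It does not subtract the change in cortical alpha while the lids are shut.

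The setting makes unequal closure plausible. The Go-NoGo task lasts 16 min in a low-light room, pictures last 100 ms, and nothing need be watched between trials. Closures could therefore cluster in the response-free phases. Alpha would then be higher there with no recovery process at work, in the direction the study expects to find.

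At stake is the interpretation of the phase question within main hypothesis (ii). The Discussion says the framework will distinguish parameters specific to sustained attention from broader influences. For the alpha phase contrast it cannot do so while eye state is unmeasured.

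**Working it through.** **No planned figure to reproduce.** The article gives no power calculation, alpha effect size, closure rate or eyes-closed/eyes-open alpha ratio. From the document come only n = 120 ("will include 120 geriatric participants"), the task length ("Sustained attention will be measured with a 16-min cued Go-NoGo task on a computer") and the 100 ms picture. Everything else below is an assumption, shown as a range.

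**1. Phase contrast in closed form.** Let f_i and f_p be the shares of time with lids closed in inter-trial and performance phases, and R the eyes-closed/eyes-open alpha ratio. With no true phase difference,

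apparent ratio = (1 + f_i(R − 1)) / (1 + f_p(R − 1)).

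With performance-phase closure at 0.3 of the inter-trial rate:
- f_i = 5%, f_p = 1.5%, R = 3: 1.10 / 1.03 = 1.068, about +7%.
- f_i = 20%, f_p = 6%, R = 4: 1.60 / 1.18 = 1.356, about +36%.

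Other combinations:

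| f_i / f_p | R = 1.2 | R = 1.5 | R = 2 | R = 3 |
|---|---|---|---|---|
| 5% / 5% | 1.00 | 1.00 | 1.00 | 1.00 |
| 10% / 2% | 1.02 | 1.04 | 1.08 | 1.15 |
| 20% / 5% | 1.03 | 1.07 | 1.14 | 1.27 |

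**2. Would this show as a significant phase difference?** Simulation with n = 120, 2,000 runs per setting, no true effect, segment noise SD 0.1 log units, paired t-test on log alpha at two-sided 5%:
- 10% extra inter-trial closure: significant in 92–94% of runs at R = 1.5 and about 100% at R = 2 to 3.
- 5% extra: 43–44% at R = 1.5 and 93–100% at R = 2 to 3.

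**3. Link between alpha and omissions across patients.** Same simulation, 80 Go trials, 5% misses with eyes open, every target missed with lids closed, between-patient SD of log alpha 0.3 to 0.6, Spearman test:
- Closure only between trials: mean correlation about 0, significant in 4.7–5.7% of runs, which is nominal.
- 5% closure at the stimulus: correlation 0.02–0.12, significant in 6–27%.
- 10% closure at the stimulus: correlation 0.05–0.26, significant in 9–83%. The top of the range needs R = 3 and the smaller between-patient spread.

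**4. Within a patient.** If a share c of Go pictures falls during closure and 5% are missed with eyes open, the closed share among misses is c / (c + (1 − c) × 0.05). For c = 2% this is 0.02 / 0.069 = 0.29. The missed/hit alpha ratio is then 1 + 0.29(R − 1): 1.14 at R = 1.5 and 1.58 at R = 3.

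**5. Eyes-open data only.** In the setting with R = 3, 10% closure at the stimulus and 10% extra between trials, restriction to eyes-open data gives a phase ratio of 1.00. A false phase difference appears in 3.9% of runs and a false omission link in 5.4%, both about nominal.

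**The case against.** Four arguments count against the point.

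**The size is assumed.** The documents do not show that closure is more frequent between trials, and with equal closure the bias is nil. This stands: it is a risk of unknown size, not a demonstrated error.

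**Level is not change.** The simulated false positives concern a difference in alpha level between phases. Section 2.5.4 asks where the largest changes occur, and research question (ii) asks whether the correlation with performance differs by phase. A closure difference that is constant over the task need not produce either. This stands as a limit on step 2. It does not help if closures become more frequent late in the task.

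**The article is condensed.** Segment rejection is often left to a fuller document, and the Discussion promises particular attention to data quality. But the article spells out its route and makes it the basis of all band analyses. The data-quality passage again relies on component removal and visual inspection.

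**Closed lids are low vigilance.** A target missed with closed lids is a real lapse, so excluding closures from the main analysis would remove part of the construct. This stands and shapes the fix.

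A reader might infer that closure between trials alone creates a false link between alpha and missed targets. It does not: step 3 gives a correlation of about 0. A reader might also correlate omissions with the relax-minus-performance alpha contrast and find a link in about 70% of simulated studies (5% mean closure, R = 3). That needs the same eyes-open omission rate in every patient. With omissions of 5% (SD 5%) it falls to 36–40%, and with 10% (SD 10%) to 18%. The article does not state that test. For pooled alpha the same setting gives only 5–11%. Median reaction time on correct Go trials excludes missed targets, so it is not directly affected by them.

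**Conclusion.** The point holds as a cheap improvement. As written, the route to task alpha cannot separate a phase difference in alpha from a phase difference in lid closure, and unequal closure would push the result towards the hypothesis. Under the stated assumptions the shift runs from nil (equal closure) through about +7% to about +36%. At n = 120, small shifts can already be significant as a level difference between phases.

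The effect on the alpha–omission association is secondary. It needs closures that extend into the 100 ms picture, and across patients it is weak for pooled alpha unless such closure is common. There the issue is not that the misses are false, but that the alpha rise would be read as a neural marker of attention when it may mark eye state.

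The documents do not support saying that hypothesis (ii) is uninterpretable. The study is explorative, and section 3.1 already warns of fatigue-related fluctuation and rules out causal attribution of EEG changes between T1 and T2.

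**What to change.** In sections 2.5.2 and 2.5.4:

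- Mark lid closures from the below-eye EOG and frontal channels before ocular components are removed.
- Report closure share by trial phase, task quarter, visit and hit/miss. Each patient's own rest recordings give the eyes-closed/eyes-open alpha ratio, so the likely size of the bias can be estimated from study data.
- Keep the all-segment analysis. Pre-specify a repeat of the phase and alpha–performance analyses on eyes-open segments, or with closure share as a covariate, as a sensitivity analysis.
- State that inter-trial alpha will be interpreted as recovery only if it persists in that analysis.

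The cost is one scripted marking step on signals already recorded. The sensitivity analysis will lose some segments, mostly from the least vigilant patients, which is why the all-segment analysis stays alongside it.

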Given the critical role of sustained attention in everyday life and the changes associated with aging, it is important to further investigate how sustained attention is reflected in EEG measures, including ERPs and power spectral changes in the frequency bands. Although these electrophysiological parameters have been associated with attentional processes, their clinical relevance as surrogate markers of sustained attention, particularly in neurogeriatric populations, remains insufficiently established.

Sustained attention in older populations is embedded within a broader biopsychosocial context. Sleep disturbances and poor sleep quality have been linked to reduced cognitive performance and reduced health-related quality of life (HrQoL) in aging cohorts (Costa et al., 2022; Sella et al., 2023). Affective symptoms such as depressive and anxiety states are associated with broad cognitive impairment, including reduced attentional control, executive functioning, memory and processing speed (Forbes et al., 2024). Moreover, subjective cognitive complaints (SCC) frequently diverge from objective measures but are clinically relevant for everyday functioning. Therefore, in addition to behavioral and electrophysiological measures, the present study includes assessments of fatigue, sleep quality, HrQoL and SCC to more comprehensively characterize sustained attention in aging.

The following research questions are thus defined for this study:

(i) Is there a correlation between sustained attention and ERPs, N200 and P300, of the EEG in latency and amplitude?

(ii) Is there a correlation between sustained attention and EEG power in the alpha and theta range? It will be tested if the correlations observed in the initial or final phases of the task differ from those observed over the entire task duration. Additionally, the hypothesis will be tested as to whether the correlation between SA and power varies between the performance phase of the task or rather the inter-trial (reset and relax) phases.

(iii) Does sustained attention improve after an inpatient multiprofessional complex treatment? If yes, is this reflected by changes in the ERPs/power spectrums of the EEG?

(iv) What are the associations between parameters of cognition, processing speed, mental fatigue, HrQoL and self-assessment of cognitive abilities, respectively, and ERPs/power spectrums of the EEG?

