### Participants

2.2

Participants will be neurogeriatric, defined as > 70 years with a primary neurological disease [participants between 50 and 69 years of age can also be included if they have at least two chronic diseases (> 6 months)] [ Sieber, 2007; Maetzler et al., 2016; Johnston et al., 2019). Other inclusion criteria are the ability to consent to the study and, if applicable, the consent of the legal representative, as well as at least 5 points on the Montreal Cognitive Assessment (MoCA, (Nasreddine et al., 2005)].

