## Discussion

3

Although attention is one of the six central cognitive domains and a fundamental function required for many other cognitive processes (Falkai et al., 2018), and studies on sustained attention across different age groups show significant differences in performance and neural dynamics in older adults (McAvinue et al., 2012; Langner and Eickhoff, 2013; Fortenbaugh et al., 2015), research on this topic in the neurogeriatric field is rare. The study presented here will investigate whether EEG has the potential to provide objective and quantitative surrogate markers of sustained attention in neurogeriatric patients. In particular, we aim to determine possible EEG changes during active task performance and during inactive (“recovery”) phases. These findings may help to elucidate pathomechanisms underlying sustained attention deficits, with potential therapeutic implications.

The strength of our proposed study lies in investigating a typical neurogeriatric population at a university hospital, covering a wide range of neurological conditions and cognitive abilities. Furthermore, the protocol employs a comprehensive multimodal assessment strategy. Sustained attention will be examined using three complementary paradigms, the cued Go-NoGo task, the PVT, and the AKT, thereby capturing sustained attention across computerized reaction-time paradigms as well as a conventional paper–pencil format commonly used in geriatric settings. Within these tasks, sustained attention will be quantified not only by mean reaction times but also through omission and commission errors, and intra-individual reaction time variability, reflecting complementary aspects of vigilance performance.

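### Fixed bands split at 8 Hz cannot separate a slowed alpha peak from a change in alpha or theta power, so the peak frequency should be extracted and the power correlations re-tested with it

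*Protocol article*

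**What the plan says.** Hypothesis (ii) in the abstract is that sustained attention "correlates with EEG power". Research question (ii) in the Introduction narrows this: "Is there a correlation between sustained attention and EEG power in the alpha and theta range".

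Section 2.5.4 computes Welch spectra "with further processing by the FOOOF (Fitting Oscillations and One Over F) package" and uses the result to "extract power values in predefined frequency bands (delta 1–4 Hz, theta 4–8 Hz, alpha 8–13 Hz, and beta 13–30 Hz". Theta and alpha therefore meet at 8 Hz for everyone. The same section gives a direction for alpha: it asks "particularly if increased alpha band activity is associated with decreased task performance".

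The cohort in section 2.2 is "defined as > 70 years with a primary neurological disease", or aged 50–69 with at least two chronic diseases, and needs "at least 5 points on the Montreal Cognitive Assessment". The Discussion describes it as "covering a wide range of neurological conditions and cognitive abilities". Sections 2.3 and 2.4.4 plan 5 minutes of resting EEG with eyes closed.

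The article uses alpha peak frequency nowhere as a band anchor, an outcome or a covariate.

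**The concern.** A band-power value answers a question about power only if the rhythm lies inside the band. A patient whose alpha peak sits at 7.5 Hz has most of that rhythm recorded as theta, and the 8–13 Hz value holds only its upper flank. Removing the aperiodic background with FOOOF does not change this, because the band limits stay where they are.

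If patients with slower peaks also attend less well, a difference in frequency alone lowers their alpha value and raises their theta value. The correlations of hypothesis (ii) would then carry a slowing component that the planned outputs cannot separate from power. The question matters here because the cohort is old, neurologically ill and cognitively very mixed, and because the study wants to propose EEG parameters as surrogate markers of attention.

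**Working it through.** **Inputs from the article.** Theta 4–8 Hz, alpha 8–13 Hz (2.5.4); N = 120 (abstract); 500 ms trial segments (Figure 3 legend). The article has no figure of its own to reproduce: it states no power basis for N = 120 and no alpha peak frequencies for this cohort.

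**Assumed.** Mean alpha peak 8.5–10 Hz; between-patient SD 0.7–1 Hz; correlation of peak frequency with attention 0, 0.3 or 0.5, with attention scored so that higher is better.

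**Step 1: where one peak's power goes.** For a Gaussian peak with centre f and width σ, the share in alpha is Φ((13 − f)/σ) − Φ((8 − f)/σ), and the share in theta is Φ((8 − f)/σ) − Φ((4 − f)/σ). With σ = 1 Hz and f = 7.5: alpha = Φ(5.5) − Φ(0.5) = 1.00 − 0.69 = 0.31.

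| Centre (Hz) | In alpha | In theta |
|---|---|---|
| 10 | 98% | 2% |
| 9 | 84% | 16% |
| 8.5 | 69% | 31% |
| 8 | 50% | 50% |
| 7.5 | 31% | 69% |
| 7 | 16% | 84% |

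At 7.5 Hz the theta share is 75% for σ = 0.75 and 62% for σ = 1.5.

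**Step 2: effect on the correlations.** Simulation with 20,000 patients per setting. True alpha and theta power are independent of attention; only peak frequency is correlated with it. Band power is the log mean of the aperiodic-free spectrum in the fixed band. Each range spans an SD of log power of 0.5 and 0.8.

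| Mean peak, SD (Hz) | Peak–attention r | Spurious r, alpha | Spurious r, theta |
|---|---|---|---|
| 8.5, 1 | 0.3 | +0.17 to +0.21 | −0.16 to −0.22 |
| 9, 1 | 0.3 | +0.13 to +0.16 | −0.17 to −0.20 |
| 8.5, 1 | 0.5 | +0.28 to +0.33 | −0.28 to −0.36 |
| 9, 1 | 0.5 | +0.19 to +0.27 | −0.28 to −0.34 |
| 10, 0.7 | 0.3 | +0.01 to +0.03 | −0.06 to −0.09 |
| 10, 0.7 | 0.5 | +0.03 to +0.04 | −0.12 to −0.16 |
| any of these | 0 | 0.00 (±0.01) | 0.00 (±0.01) |

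Alpha power taken at each patient's own peak correlates 0.00 (±0.01) with attention in every setting. If spectra are computed per 500 ms segment (resolution 1/0.5 s = 2 Hz), the pattern is similar: for a mean of 9 Hz and r = 0.3, alpha +0.10 to +0.14 and theta −0.16 to −0.21.

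**Step 3: scale.** At N = 120 the nominal two-sided 5% threshold is 1.98/√(118 + 1.98²) ≈ 0.18. The correlation detectable with 80% power is tanh((1.960 + 0.842)/√117) = 0.253. An artefact of 0.13 to 0.22 is of that order; one of 0.01 to 0.04 is negligible.

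**The case against.** The strongest reply is that the decisive premise is not in the article. No section says that alpha peaks in this cohort lie near 8 Hz or that they track attention. The only alpha frequency mentioned, in the Introduction, is about 10 Hz and comes from a cited study; at 10 Hz, 98% of the peak is in band. This stands. A reader might infer that the alpha and theta correlations in this cohort do partly measure slowing. The documents support only that they would, if both conditions hold.

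A reader might also infer that one frequency shift would confirm hypothesis (ii) in both bands. The abstract's hypothesis has no direction, so either sign could count. But section 2.5.4 looks in particular for higher alpha with worse performance, and the artefact pushes alpha the other way. It could mask that effect as well as create a correlation.

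Three further limits stand.

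- **Adjustment.** The regressions in the Discussion adjust for MoCA, age and affective symptoms, which absorbs the part of slowing those variables explain. It is not stated for the plain correlations, and the ANCOVA in section 2.5.1 names N200 and P300, not band power.
- **Within-patient contrasts.** Performance versus inter-trial phases are affected less if a patient's peak is stable. The claim that a T1–T2 change in power could really be a change in frequency is possible but was not computed.
- **Type of power value.** The shares in Step 1 assume that power is averaged across the band. If FOOOF's fitted peak power is used, only peaks centred below 8 Hz change band: Φ((8 − 9)/1) = 16% of patients at a mean of 9 Hz, Φ((8 − 8.5)/1) = 31% at 8.5 Hz. The article does not say which is meant.

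Finally, fixed bands are conventional and the study is exploratory. That argues for keeping them. It does not help a reader who must tell slowing from power.

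**Conclusion.** The point holds as a conditional limit on interpretation, not as an internal contradiction. Fixed bands split at 8 Hz assign part of a slow alpha rhythm to theta; that follows from the band limits alone. Whether it biases hypothesis (ii) depends on two things the article does not give: how many patients have peaks near or below 8 Hz, and whether peak frequency is related to attention. Over the assumed range the artefact runs from zero to a size comparable with the smallest correlation the study could detect. The planned adjustment removes only part of it. As written, the study would report a band-power correlation without the one variable needed to say whether it reflects power.

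The evidence does not support replacing the primary bands with bands anchored to the individual peak. With a peak at 7.5 Hz and alpha set from 2 Hz below to 3 Hz above it, alpha becomes 5.5–10.5 Hz. A 4 Hz wide theta band directly below would be 1.5–5.5 Hz, overlapping the protocol's 1–4 Hz delta band. That exchanges one misassignment for another.

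**What to change.** In section 2.5.4, keep the fixed bands as the conventional analysis and add:

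1. From the FOOOF fit of the 5-minute eyes-closed rest (posterior channels), extract each patient's alpha centre frequency and the aperiodic-adjusted alpha power at that peak. Flag patients with no detectable peak.
2. Report peak frequency as a marker of its own at T1 and T2.
3. Repeat the alpha and theta correlations with attention using peak-anchored alpha power, and with peak frequency as a covariate.
4. Interpret a fixed-band correlation as a power effect only if it persists in step 3.

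The recording and the software are already planned, so the cost is one extra processing step. The downside is that some patients will have no detectable peak and drop out of the peak-based analyses; their number should be reported.
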